### Study population and recruitment

2.2.

Participants were recruited at the end of pregnancy (when admitted to the obstetric ward) or within one week after birth in case of hospitalized infants at HULAFE. Recruitment started in October 2020 and was completed in July 2022. Three mother-infant groups were enrolled, i.e., PI fed with OMM (PI-OMM), PI fed with pasteurized DHM (PI-DHM), and TI receiving OMM (TI-OMM), and their mothers.

The inclusion criteria were (i) acceptance of the mother to participate and sign an informed consent form, (ii) a gestational age <32 weeks for the group of PI and >37 weeks for the group of TI, and (iii) exclusive consumption (i.e., >80% of total intake) of either OMM or DHM at time point CEN (complete enteral nutrition, 150 mL/Kg/day) for PI or RBW (recovery of birth weight) for TI. Although the type of feeding of PIs included in either group (PI-OMM or PI-DHM) may have changed at later time points, they remained in the same study group, so the effect of feeding of each type of milk at CEN and its long-term effects can be studied. Likewise, the use of infant formula and the initiation of weaning at later time points was recorded without affecting follow-up assessments. The exclusion criteria were (i) non-compliance with any of the inclusion criteria, (ii) the requirement of a special diet for the mother (e.g., celiac disease, diabetes) or maternal consumption of probiotics, (iii) the need of intestinal surgery, severe congenital malformations, or chromosomopathies of the infant, (iv) mother's residence outside the Valencian Community and (v) severe language barriers hampering the collection of necessary data from mothers not speaking Spanish and/or English.

Sample size estimation was performed for the primary outcome (i.e., % weight gain/month from birth until hospital discharge of PI fed with DHM and OMM) and was based on result of a previous study (42). Considering the median % weight gain/month (interquartile range, IQR) of 52% (IQR: 30) in the PI-DHM group and 63% (IQR: 21) in the PI-OMM, 18 infants per group were needed to achieve a power of 90% with an alpha error of 5% between the % weight gain/month of PI exclusively receiving either OMM or DHM at CEN.

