### Statistics and data integration

2.7.

The Student's *t*-test, Wilcoxon ranksum test or *Χ*^2^ test with *α* = 0.05 will be used for between-group comparisons and fold changes (FC) will be calculated as the ratio of means or medians between groups in accordance to the underlying distribution of the data. Pearson's linear or Spearman rank correlation coefficients will be determined between continuous variables. If necessary, partial correlation coefficients adjusting for known confounding factors will be computed. The false discovery rate (FDR) from the *p*-values of multiple-hypothesis testing will be estimated using the Benjamini and Hochberg procedure (86) and adjusted *p*-values <0.05 will be considered statistically significant.

One of NUTRISHIELD secondary objectives is the development of a personalized nutrition system based on measured biomarkers. The system is to be made available to medical personnel, as well as mothers, to improve infant-mother dyads' health and wellbeing. The results and the associations revealed from the study will be used to train a personalized nutritional algorithm with data obtained from clinical settings. This will be used to build and validate the NUTRISHIELD platform, describing how a theoretical framework designed and fed by the patients' data translates to clinical practice. Toward that goal, a comprehensive data integration system has been developed as the Clinical Trial App (CTA). The CTA is a system intended for personalized medicine/nutrition, implementing the following main features: (i) data acquisition from questionnaires, (ii) data acquisition from laboratory biomarker analysis, (iii) processing data to train machine learning algorithms, and (iv) deploying trained algorithms to produce reports for final users.

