## Results and discussion

3.

Figure 4 summarizes the recruitment process, including the eligible PI (*n* = 104), excluded (*n* = 49), lost to follow up (*n* = 10) and the number of PI that were finally included in the study (*n* = 45). In addition, a control group comprising 31 full term OMM infant-mother dyads was recruited, with five participants being lost during follow-up. Altogether, a total of 71 infant-mother dyads were included and completed the study (28 PI-OMM, 17 PI-DHM and 26 TI-OMM), after losing 15 infant participants during follow-up. In total 662 urine, 594 faeces, 134 buccal swab, 33 venous and arterial cord blood, and 234 HM samples, as well as aliquots from 147 DHM batches before and after pasteurization have been collected. An ample array of laboratory methods for biomarker analysis and screening of biological samples and three *ad-hoc* designed sensors were developed. Currently, the analysis of all collected study samples is in progress at the different participating institutions.

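### The eligibility list does not exclude siblings and the named tests assume independent infants; if siblings sit in the same milk group, the PI-OMM versus PI-DHM test is too liberal

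*Protocol article*

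**What the plan says.** Section 2.2 (Study population and recruitment) sets three inclusion and five exclusion criteria. Gestational age is the main infant criterion: "a gestational age <32 weeks for the group of PI and >37 weeks for the group of TI". The infant-level exclusions are "the need of intestinal surgery, severe congenital malformations, or chromosomopathies of the infant". Neither list mentions singletons, twins or multiples. Milk group is set by what makes up more than 80% of an infant's intake at complete enteral nutrition.

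The primary outcome is the percentage "weight gain/month from birth until hospital discharge of PI fed with DHM and OMM". The sample size is in infants: "18 infants per group were needed to achieve a power of 90% with an alpha error of 5" per cent.

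For analysis, section 2.7 says that Student's t-test, the Wilcoxon rank-sum test or the chi-square test "will be used for between-group comparisons and fold changes (FC) will be calculated as the ratio of means or medians between groups". Besides false-discovery-rate control, the only adjustment named is this: "If necessary, partial correlation coefficients adjusting for known confounding factors will be computed".

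Section 3 (Results and discussion) reports 45 preterm infants included and says that "a total of 71 infant-mother dyads were included and completed the study", made up of 28 PI-OMM, 17 PI-DHM and 26 TI-OMM. The number of distinct mothers is not given.

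**The concern.** As the criteria are written, a twin pair born before 32 weeks is eligible. Siblings share a mother, a gestational age and a neonatal unit, and also the milk supply that largely decides the milk group. They would therefore usually, though not always, fall in the same group, and their weight gains are likely to be positively correlated.

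The t-test and rank-sum test give each infant the weight of an independent observation. With correlated siblings in the same group, the standard error of the difference comes out too small and the p-value too optimistic. This concerns the primary outcome, which has one value per infant, so it is separate from the repeated sampling over time. Neither false-discovery-rate control nor partial correlation deals with it.

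The secondary analyses have a related exposure. They relate maternal diet, psychosocial status and milk composition to one another and to infant data. If the data set has one row per infant, a mother of two enrolled infants would enter her own diet, stress and milk values twice.

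**Working it through.** **The plan's own figure.** Section 2.2 assumes medians of "52% (IQR: 30) in the PI-DHM group and 63% (IQR: 21) in the PI-OMM" group. With SD = IQR/1.349, the SDs are 22.2 and 15.6, with root mean square 19.2. For a difference of 11 points, two-sided 5% and 90% power, n = 2 × 19.19² × (1.960 + 1.282)² / 11² = 64 per group. The stated 18 does not reproduce, even before any clustering. That is a separate issue and is not argued here; the calculation below does not depend on it.

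**Inputs.** From the documents: 17 PI-DHM and 28 PI-OMM infants, and alpha 5% (two-sided assumed). Not in the documents, hence assumed:
- f, the share of infants in a twin pair within one group: 0.1 to 0.4
- ρ, the sibling correlation of the outcome: 0.3 to 0.9

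**Variance.** If a share f of a group's infants are in same-group pairs, the variance of the group mean is multiplied by about 1 + fρ:
- f = 0.1, ρ = 0.3: 1.03
- f = 0.3, ρ = 0.5: 1.15
- f = 0.4, ρ = 0.9: 1.36

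A ratio of 1.36 means that the naive variance is 1 − 1/1.36 = 26% too small and the naive standard error 1 − 1/√1.36 = 14% too small. At 1.03 the figures are 3% and 1.5%.

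**Type I error.** The table simulates the pooled t-test with 17 v 28 infants, equal SD and no true difference (100,000 runs per cell).

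| Twin pairs (PI-DHM + PI-OMM) | Share of the 45 infants | ρ = 0.3 | ρ = 0.5 | ρ = 0.9 |
|---|---|---|---|---|
| 0 + 0 | 0% | 5.0% | 5.0% | 4.9% |
| 1 + 1 | 9% | 5.4% | 5.7% | 6.1% |
| 2 + 3 | 22% | 5.8% | 6.3% | 7.5% |
| 3 + 4 | 31% | 6.1% | 7.0% | 8.6% |
| 3 + 6 | 40% | 6.4% | 7.4% | 9.3% |

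The large-sample formula 2 × [1 − Φ(1.96/√(1 + fρ))] gives 5.3% at (0.1, 0.3) and 9.3% at (0.4, 0.9), in agreement with the simulation.

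**Siblings split between groups.** With three pairs divided between PI-DHM and PI-OMM, the rejection rate is 4.5% at ρ = 0.3 and 3.7% at ρ = 0.9. The test is then conservative.

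**Check against the article's counts.** Mothers and infants give buccal swabs at month six (section 2.3), and 134 were collected (section 3). Assume at most one swab per person and only from completing dyads. With 71 distinct mothers there are 142 people, so 134 is 94% complete. Each preterm twin pair removes one mother:
- 5 pairs (22% of preterm infants): 137 people, 98% complete
- 7 pairs (31%): 135 people, 99% complete
- 9 pairs (40%): 133 people, fewer than the swabs collected

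The top of the assumed range is therefore unlikely unless some swabs were repeats or came from dropouts.

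**The case against.** The strongest reply is that the premise is missing. The article never mentions twins or siblings, so eligibility is inferred from silence. Participants are reported as dyads, and 28 + 17 equals the 45 preterm infants, which fits one infant per mother. The swab count fits that too. This is also a condensed article, and the handling of siblings may be set out in a full protocol or analysis plan that is not shown.

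Much of this stands. Nothing shows that siblings were enrolled, and the upper end of the assumed range is strained. However, the dyad count fits equally well if each sibling was counted with the shared mother as a separate dyad. The criteria are an enumerated list with specific infant exclusions, and multiple birth is not among them. The named tests are also a stated choice: as written, they cannot accommodate siblings if there are any.

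A reader might go further and infer that the standard error of the primary comparison is too small as a matter of fact. The documents do not support that, because it needs siblings, in the same group, with positive correlation. A reader might also infer that multiples concentrate in PI-DHM because their mothers less often meet full milk need. That does not follow either. A mother who meets only part of the need may have a mixed-fed infant who passes neither 80% threshold and enters neither group.

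**Conclusion.** The point holds in conditional form. The eligibility list leaves siblings admissible, the sample size is counted in infants, and the tests named in section 2.7 ignore any correlation between siblings. If siblings were enrolled in the same milk group, the nominal 5% test of PI-OMM versus PI-DHM would run at roughly 5.4-9%, with a true variance about 1.03-1.36 times the naive one.

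That range rests on an assumed 10-40% of preterm infants in same-group twin pairs and an assumed correlation of 0.3-0.9. The swab count points to the lower or middle part of the twin share. The effect is nil without siblings and reverses if they are split between groups. This is a modest to moderate threat to the primary test whose presence the article does not let a reader determine.

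**What to change.** Before the primary analysis, count the mothers behind the 45 preterm infants and report that number beside the number of infants, by milk group. If every mother contributes one infant, a sentence saying so closes the point and the named tests can stand in this respect.

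If any mother contributes more than one infant, keep all infants and analyse the primary comparison with mother as the cluster. Either a random intercept for mother or cluster-robust standard errors with a small-sample correction will do; the correction matters with groups of this size. Both also cover siblings who fall in different groups. In mother-level and milk-level correlations, use one record per mother.

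The cost is one change to the analysis model and a slightly wider confidence interval when siblings share a group. No new data are needed beyond the link between each infant and mother. Recruitment is closed and sample analysis is still in progress, so the count can be made before results are known.

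### Student's t-test pools variances, although the planning figures suggest that the smaller preterm group (PI-DHM) is the more variable; Welch's test would be a safer primary test

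*Protocol article*

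**What the plan says.** Section 2.7 (Statistics and data integration) of the protocol article lists Student's t-test, the Wilcoxon rank-sum test and the chi-square test at an alpha of 0.05. It says that these "will be used for between-group comparisons and fold changes (FC) will be calculated as the ratio of means or medians between groups", followed by "in accordance to the underlying distribution of the data". No unequal-variance form of the t-test is named.

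Section 2.2 (Study population and recruitment) defines the primary outcome as % "weight gain/month from birth until hospital discharge of PI fed with DHM and OMM". The planning values are medians of "52% (IQR: 30) in the PI-DHM group and 63% (IQR: 21) in the PI-OMM". The sample size "was based on result of a previous study", and the stated result is that "18 infants per group were needed to achieve a power of 90% with an alpha error of 5"%.

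Section 3 (Results and discussion) gives the dyads that completed the study as "28 PI-OMM, 17 PI-DHM and 26 TI-OMM". The spread of weight gain in this cohort is not reported.

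**The concern.** Student's t-test estimates one common variance, in which the larger group carries more weight. When the smaller group is the more variable one, that estimate leans towards the smaller variance. The standard error of the difference then comes out too small, the confidence interval too narrow and the p-value too low.

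The article's own figures point to this configuration for the primary contrast: 17 infants with a planning IQR of 30 against 28 infants with a planning IQR of 21. At stake is whether the nominal 5% level and 95% interval for PI-DHM versus PI-OMM mean what they say.

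**Working it through.** **Inputs.** Planning IQRs of 30 (PI-DHM) and 21 (PI-OMM) and planned n = 18 per group, from section 2.2. Completers of 17 and 28, from section 3. Assumed: normal data, so SD = IQR/1.349; a two-sided test, since sidedness is not stated; and completers as the analysis set.

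**The plan's own figure.** Pooled as a root mean square, the SD is √[(22.24² + 15.57²)/2] = 19.19. The normal formula is n = 2(1.960 + 1.282)² × 19.19²/11², where 11 = 63 − 52. This gives 64 per group, so the stated 18 is not reproduced under this reading of the IQRs. That is a separate matter. The calculation below uses only the ratio of the spreads and the group sizes.

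**Spreads.** SD(DHM) = 30/1.349 = 22.24. SD(OMM) = 21/1.349 = 15.57. Ratio = 30/21 = 1.43.

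**Standard error at 17 and 28.**
- True: √(22.24²/17 + 15.57²/28) = √(29.09 + 8.65) = 6.14 points.
- Pooled variance: (16 × 22.24² + 27 × 15.57²)/43 = 336.2.
- Pooled SE: √[336.2 × (1/17 + 1/28)] = 5.64 points.
- Ratio: 5.64/6.14 = 0.918, so the pooled SE is about 8% too small.

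**95% half-width.** Pooled, 43 df: 2.017 × 5.64 = 11.4 points. Welch, about 25.6 df: 2.057 × 6.14 = 12.6 points.

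**Type I error, large-sample formula.** 2 × [1 − Φ(1.96 × 0.918)] = 7.2%.

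**Type I error by simulation** at 17 and 28, SD ratio 1.43, normal data (200,000 runs for the t-tests, 100,000 for Wilcoxon):

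| Test | Type I error |
|---|---|
| Student's t | 7.15% |
| Wilcoxon, read as a location test | 6.1% to 6.5% (with or without continuity correction) |
| Shapiro test, then t or Wilcoxon (20,000 runs) | 6.9% |
| Welch's t | 5.0% |

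**Dependence on the assumed spread ratio**, Student's t at 17 and 28:

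| SD ratio | 1.0 | 1.2 | 1.43 | 1.75 | 2.0 |
|---|---|---|---|---|---|
| Type I error | 4.9% | 6.1% | 7.15% | 8.4% | 9.3% |

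**Dependence on shape**, ratio 1.43. With heavier-tailed data (t with 5 df), Student's t gives 7.1% and Welch 4.8%. With skewed lognormal data and equal means, they give 7.1% and 5.7%.

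**At the planned 18 and 18**, ratio 1.43. The pooled and unpooled standard errors are algebraically identical when the groups are equal in size. Student's t runs at 5.1% and Wilcoxon at 4.9% to 5.3%.

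**Cost of Welch if the spreads are equal.** At 17 and 28 with a true difference of 0.8 SD, simulated power is about 72% for Student's t and 71.5% for Welch.

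**The case against.** The strongest reply is that the 7% is not a property of the plan as written. It joins spreads from an earlier study to completer counts from this one. If the spreads here are equal there is no inflation, and the balanced design that was planned would have given none either. This stands, and it is why the figure can only be stated conditionally.

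The completers may also not be the analysis set. The primary outcome ends at hospital discharge. Section 3 implies 104 − 49 = 55 preterm infants before 10 were lost to follow-up, and some of those 10 may have discharge weights. Their split by group is not in the text. This stands too.

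A third reply is that pooled versus unpooled variance is a detail for the analysis plan. This stands in part: the article does not rule out Welch. But it does not leave the test open either. It names Student's test, which is the equal-variance one.

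Three stronger readings are tempting, and the documents do not support them:
- **Choosing the test from the data causes the inflation.** A choice based on a normality test gives 6.9%, no worse than Student's t alone. The phrase about the distribution of the data may also refer only to means or medians in the fold change.
- **Wilcoxon shares the 7%.** With symmetric data it is about 6%. It is also valid for the null of identical distributions, and unequal spread matters only when it is read as a test of location.
- **The same weakness affects DHM batches compared with OMM samples.** The article gives no spread for either, so even the direction of any effect is unknown.

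**Conclusion.** The point holds as a conditional one of modest size. For the primary PI-DHM versus PI-OMM contrast, Student's t would run about 2 percentage points above its nominal 5% level, and its 95% interval would be about 1.2 points too narrow on each side (12.6 − 11.4). This rests on three assumptions: that the earlier study's spreads carry over to this cohort, that the 17 and 28 completers are the infants analysed, and that the data are roughly normal. The first matters most: the error moves from 4.9% at equal spreads to 9.3% at a ratio of 2.0.

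A reader might infer that the primary comparison does run at 7%. The documents do not show that, because this cohort's spread is unreported. They do show that the named test is exposed in the direction their own planning figures suggest, and that a named alternative removes the exposure almost free of charge.

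**What to change.** In section 2.7, or in the analysis plan before the weight data are compared, name Welch's unequal-variance t-test on % weight gain/month as the primary PI-DHM versus PI-OMM test. If the comparison is adjusted, use regression with heteroscedasticity-robust (HC3) standard errors instead. Keep Wilcoxon as a sensitivity analysis, and use Welch in place of Student's t for the other two-group comparisons of means. State which infants form the primary analysis set.

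This takes a sentence or two and no new data. Intervals become somewhat wider if the spreads differ as planned, and about half a percentage point of power is lost if they do not differ.

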### Assessment points and biological samples

2.3.

Samples from lactating mothers and their infants are collected at different timepoints, as shown in Figure 1. At birth, cord blood, and urine, and faeces from both infants and mothers are collected when possible. When PIs achieve CEN and TIs RBW, as well as one, two, three, and six months after delivery, urine and faeces from mothers and infants, as well as, HM from lactating mothers, are collected. Infants' and mothers' buccal swabs are collected at month six. During hospitalization of participants, samples are collected at the hospital by healthcare providers. After discharge, samples are collected at home and either transported to the hospital by study participants or staff of the NUTRISHIELD study. Mothers receive Standard Operation Procedures (SOPs) with detailed instructions and all the required material for sample collection at home. Additionally, hospital's staff instructs mothers on how to collect and store samples correctly.

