### Dietary and psychological status assessments

2.4.

For all three study groups, information obtained from clinical records is collected. Anthropometric data (e.g., weight, height, and head circumference), sociodemographic, dietary, other relevant information related to lifestyle (e.g., smoking habits, sleep hours, and physical activity), and psychosocial status are provided through questionnaires by participating mothers as summarized in Table 1. As shown in Figure 1, 24 h dietary recalls are recorded at all timepoints except at birth, food frequency questionnaire (FFQ) at month 1, maternal psychosocial status at CEN/RBW and month six (corrected age for PI groups), and infant neurodevelopment at months six and twenty-four. The questionnaires are administered online, on paper, or through direct interviews with the mothers.

**Table 1 T1:** Recorded parameters from lactating mothers and infants.

Assessment	Parameter
Nutrition	FFQ
	24-hour dietary recall
Clinical data	Maternal conditions
	Pregnancy complications
	Delivery type
	Medical information
	Maternal medication
	IIFAS
	Infant's gestational age
	Infant sex
	Infant diagnosis
	Perinatal complications
Sociodemographic data	Origin
	Education
	Household income
	Employment status
Lifestyle	Smoking habits
	Physical activity
	Sleeping habits
Anthropometric data	Maternal weight
	Infant height
	Infant head circumference
Psychosocial status	MSPSS
	FACES
	PSS-10
	STAI
	EPDS
	BDI
	TEQ
	PBQ
	PSI
Infant neurodevelopment	ASQ-3
	IBQ
	Merril-Palmer revised scales

FFQ, Food Frequency Questionnaire; IIFAS, Iowa Infant Feeding Attitude Scale; BMI, Body Mass Index; MSPSS, Multidimensional Scale of Perceived Social Support; FACES, Family Adaptability and Cohesion Evaluation Scale; PSS-10, Perceived Stress Scale-10; STAI, State-Trait Anxiety Inventory; EPDS, Edinburgh Postnatal Depression Scale; BDI, Beck Depression Inventory; TEQ, Traumatic Experience Questionnaire; PBQ, Postpartum Bonding Questionnaire; PSI, Parenting Stress Index; ASQ-3, Ages & Stages Questionnaires; IBQ, Infant Rothbart's Temperament Questionnaire.

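### Section 2.7 names only methods for independent observations although samples are repeated within person and donor; if those samples are pooled, secondary tests at a nominal 5% could run at roughly 9–35%

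*Protocol article*

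**What the plan says.** Section 2.7 (Statistics and data integration) gives the whole inferential toolkit in one paragraph. Student's t-test, the Wilcoxon rank-sum test or a chi-squared "test with *α* = 0.05 will be used for between-group comparisons". For associations, "Pearson's linear or Spearman rank correlation coefficients will be determined between continuous variables". The one extension is "If necessary, partial correlation coefficients adjusting for known confounding factors will be computed". Multiplicity is handled by Benjamini-Hochberg, and "adjusted *p*-values <0.05 will be considered statistically significant". No method for repeated measures is named.

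The data are longitudinal. Section 2.3 schedules collection at complete enteral nutrition or recovery of birth weight, "as well as one, two, three, and six months after delivery, urine and faeces from mothers and infants", with mothers' milk at the same visits. That makes up to five milk samples per mother. Urine and faeces are also taken at birth where possible. Section 3 reports 662 urine samples, 594 faeces samples and "33 venous and arterial cord blood, and 234 HM samples", with 71 dyads completing (28 + 17 + 26).

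Exposures differ in how often they are measured. Section 2.4 places the "food frequency questionnaire (FFQ) at month 1", so it and the Mediterranean diet score take one value per mother. The 24 h recall is repeated at every milk time point. For donors, the stress scale (PSS-10) is taken once, at entry, and is to be correlated with milk compounds; the donor FFQ is repeated for each batch. Section 2.3 says that donor collection times relative to delivery vary, and Section 3 counts 147 batches.

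**The concern.** Pearson, Spearman, partial-correlation and two-sample p-values are valid when each observation is an independent unit. Several samples from one mother are not. If the exposure is fixed or stable within mother and the analyte is also partly stable, a pooled correlation overstates the information available. Partial correlation adjusts for covariates, not for clustering. Benjamini-Hochberg takes the p-values as given.

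The secondary objectives on maternal diet and psychosocial status, and on microbiota and milk composition, rest on such associations. Section 2.7 also says that the associations found will train the personalised nutrition algorithm for mothers and medical staff. False associations would carry through to that product.

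Restricting each analysis to one visit avoids the problem for mothers and infants. It has no direct counterpart for donor milk, where there is no common visit and a once-per-donor stress score may face several batches from the same donor.

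**Working it through.** **The plan's own figure.** There is none to reproduce. The article gives no ICC, power or error rate for the correlations beyond the nominal 5%, taken here as two-sided. Its only sample-size statement (18 per group) concerns the primary outcome.

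**Samples per person (counts from Section 3).**
- Milk: 234/54 = 4.33 if all samples come from the 28 + 26 = 54 mothers in the own-milk groups; 234/71 = 3.30 if all 71 mothers contributed.
- Urine: 662/142 = 4.66 and faeces: 594/142 = 4.18, over 71 mothers plus 71 infants.
- Donor batches per donor: not calculable, because the number of donors is not given.

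**Formula, if samples are pooled as independent.** With *m* samples per person, exchangeable within-person correlation and no true association:

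- design effect DE = 1 + (*m* − 1) × ICC(exposure) × ICC(analyte)
- true size = 2 × [1 − Φ(1.96/√DE)]

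Worked example: a once-per-mother exposure (ICC = 1), analyte ICC 0.5 and *m* = 4.33 give DE = 1 + 3.33 × 0.5 = 2.67, and 2 × [1 − Φ(1.96/√2.67)] = 23.0%.

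All ICCs are assumptions; the documents give none.

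| ICC product | Example | Size, *m* = 3.30 | Size, *m* = 4.33 |
|---|---|---|---|
| 0 | either variable has ICC 0 | 5.0% | 5.0% |
| 0.09 | both 0.3 | 7.4% | 8.6% |
| 0.25 | both 0.5 | 11.8% | 14.8% |
| 0.30 | exposure 1, analyte 0.3 | 13.2% | 16.6% |
| 0.49 | both 0.7 | 17.9% | 22.7% |
| 0.50 | exposure 1, analyte 0.5 | 18.1% | 23.0% |
| 0.70 | exposure 1, analyte 0.7 | 22.5% | 28.3% |
| 1 | both fixed within mother (limit) | 28.1% | 34.6% |

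**Simulation check.** With 54 mothers and 4 samples each, Pearson tests rejected in 15%, 22% and 27% of runs for a once-per-mother exposure with analyte ICC 0.3, 0.5 and 0.7, and in 8% and 13% when both ICCs were 0.3 or 0.5. Spearman results were similar. With 71 mothers and 3 samples each, the once-per-mother figures were 13%, 17% and 21%.

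**One value per mother.** With 54 mothers at a single time point, the simulated size was 5.0% (Pearson) and 4.8% (Spearman).

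**Benjamini-Hochberg.** In 200 simulated independent tests with 10% true effects, the realised false discovery rate was about 4% at DE = 1, 35% at DE = 2.0 and 60% at DE = 3.3, against a 5% target.

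**The case against.** The strongest reply is that the article never says samples are pooled. A reader might infer that simple correlations are prescribed across all samples, that the tests therefore run at 17–28%, and that false-discovery control fails. The text does not support this. Correlating within each time point is fully compatible with Section 2.7 and holds 5%. The 17–28% range needs pooling, all 234 milk samples assigned to 54 mothers, and an exposure fixed within mother against an analyte with ICC of about 0.3–0.7. If the 15 participants lost to follow-up also gave milk, the denominator could be 71 + 15 = 86, which gives *m* = 2.72 and 11–19% for the same ICCs.

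Several exposures also fit the simple methods better than they first appear:
- The FFQ covers the month before it is given, so month-1 milk is its natural partner.
- Mothers' psychosocial scales are taken twice. Time-matched pairing gives at most two samples per mother, so DE cannot exceed 2 and size cannot exceed 16.6%.
- Polygenic scores are related in Section 3 to urinary biomarkers and the metabolic profile, not to milk.
- For infant vitamin status, the only infant-side material listed is cord blood, collected once.
- Known confounders, such as gestational age, can enter partial correlations.

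All of this stands, and it makes the error rate conditional. A condensed article may also leave the handling of repeated samples to a full analysis plan. But Section 2.7 is not merely silent: it commits to specific methods for a longitudinal dataset without fixing the unit of analysis. One compliant reading holds 5% and another does not. The donor correlations have no common time point to fall back on.

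**Conclusion.** The point holds in conditional form. The named methods assume independence, the sampling is repeated, and neither partial correlation nor Benjamini-Hochberg corrects for clustering.

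If repeated samples are pooled as independent, nominal 5% tests could run at roughly 9–35% with 4.33 milk samples per mother (7–28% with 3.30). For a once-per-mother exposure and analyte ICC 0.3–0.7, the range across both sample counts is 13–28%. If either variable has no within-person correlation, size stays near 5%. The figures rest on assumed ICCs, exchangeable correlation and an average number of samples per mother. For donor batches the size cannot be computed.

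The primary outcome, monthly percentage weight gain from birth to discharge, is one value per infant and is not affected by repeated sampling. Severity is moderate and limited to secondary objectives; nothing here supports treating it as a flaw in the main comparison.

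**What to change.** State the unit of analysis for every secondary association.

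- Where more than one sample per person or donor is used, fit a linear mixed model, on a transformed scale if needed. Include a random intercept for mother, infant or donor as appropriate, and fixed effects for time point and group.
- Otherwise restrict each correlation to one time point and one group. For once-per-donor exposures such as the PSS-10, use one milk value per donor.
- Apply Benjamini-Hochberg to the p-values from these analyses.

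The cost is a few sentences of plan text, routine model code and fewer nominally significant associations. Section 3 says sample analysis was still in progress, so no new data collection is needed.
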